### Planned conduct

Initial application for funding was made in September 2009, accompanied by 18 letters from hospital CEOs or other senior administrators indicating willingness for their hospital to participate. Successful re-submission in March of 2010 preceded announcement of funding in July 2010. Study resources were obtained from Canadian Institutes of Health Research (CIHR). After approval of $4 million by the reviewing panel, a budget of $3.3 million was granted. Funds were released by the CIHR in December 2010 following recruitment and approval of the three-person data safety and monitoring board, clinical trial registration (CTN#1000018562) and Research Ethics Board (REB-IRB) approval at the sponsoring institution. The study coordinating center is at the Center for Safety Research at the Hospital for Sick Children, Toronto. The study staff is supported by the infrastructure of the Child Health Evaluative Sciences Program of the Research Institute of the Hospital for Sick Children.

EPOCH REB-IRB applications sought and obtained waiver of patient-level consent (Table 6). The local documentation system is used as a part of routine hospital practice, patient-level data are retrospectively obtained and precedent exists in Canada and the UK [51,52]. Furthermore, consent for the participation of 100,000 patents is not feasible, and if required, would significantly undermine the scientific validity of the study. REB-IRB applications also seek approval of implied consent from healthcare professionals for staff surveys and the post-study survey of administrative perspectives [52]. Hospital recruitment though the networks of the CCCTG preceded the enrollment of hospitals with an identified site investigator, administrative and research ethics board approval, and it was contingent on the number of sites previously enrolled in the study. The enrolled sites and associated ethical approvals are provided in Additional file 2.

**Table 6 Tab6:** **Rationale for waived patient consent in EPOCH**

1	Consent for routine documentation practice is implied with hospital admission + this is also true for other practices including staffing, ICU consultation, physician review
	+ Documentation is an inherent and routine part of hospital care
	+ In intervention hospitals the BedsidePEWS becomes the accepted standard for documentation
	+ In control hospitals and before implementation in hospitals randomized to implement BedsidePEWS, consenting to routine care in a situation where that there is no alternative is counter-intuitive
2	Patient-level data are retrospectively obtained and + does not require patient contact
	+ does not require additional clinical investigation
	+ precedent exists for waived consent for this type of data collection
3	Preemptive consent for events (including in-hospital cardiac arrest, death) that have not occurred - and that may not occur
	+ Is potentially distressing to families
	+ Is inefficient use of research resources
4	Obtaining consent is not feasible for 100,000 patients anticipated in the study sample
	+ retrospective consent from families of deceased children may add burden and is potentially distressing to families
5	Incomplete enrollment would undermine and bias the scientific validity of the study
6	Data will be presented in aggregate.
	No identifying information will leave the study office in the participating hospital

Fifth, once completed the analyses will be reviewed by an independent statistician based at another university.

Sixth, the interpretation of the data and their reporting in iterative drafts of the main study manuscript will be a shared activity of the executive steering committee and writing committee and will be complimented by pre-submission review by independent CCCTG reviewers.

## Discussion

Preliminary data suggest that the BedsidePEWS score can identify patients at risk for near and actual cardiopulmonary arrest, can be calculated both rapidly and reliably and that its clinical implementation is associated with potential improvements in patient and process of care outcomes. The resource implications of system-wide implementation, the previous lessons from the MERIT study, and the uncertain effect on important clinical outcomes underscore the relevance of the cluster-randomized design, the selection of the intervention and the outcomes used in EPOCH. EPOCH will be conducted in 22 hospitals, involve an estimated 100,000 patients admitted for about 400,000 patient-days and describe approximately 1900 urgent ICU admissions, 200 cardiac arrest events and 500 deaths. Mortality in hospitalized children is an objective measure of quality of care and is used extensively to benchmark the performance of PICUs [58,63-66], surgical programs and hospitals [67-69].

All-cause hospital mortality was selected as the primary outcome in EPOCH for the following reasons. First, mortality is objective and can be reliably assessed. Second, a reduction in all-cause hospital mortality is the ultimate goal of any intervention to improve the outcomes of care of hospitalized children. Third, observational studies of MET-RRT have reported reduced all-cause mortality [36,38]. Fourth, several studies show that when children who have been hospitalized die, most do so in hospital [70-73]. In a 6-year study of in-ICU cardiac arrest, we found only one (1.4%) additional death after index-hospitalization discharge and within 12 months of the index cardiac arrest. Fifth, the effect of pediatric palliative care services on displacing place of death to home or hospice is small [72,74-77]. One large US study found the proportion of deaths in the hospital decreased by less than 6% (from 85.7 to 80.1%) over a 10-year period [75]. Thus, measuring hospital mortality provides a reasonably accurate measure of mortality in children who have been or are currently hospitalized.

As well, all-cause mortality is an established quality metric in Canadian and British adult hospitals and is publicly reported as the standardized mortality ratio in Ontario Hospitals [68,69,78-80]. Finally, while death ‘with DNR’ vs. ‘unexpected’ deaths (no DNR) has been used to distinguish ‘preventable’ from ‘unpreventable’ deaths following acute events in adult patients [34,81], in hospitalized children there are significant limitations to this distinction: (1) DNR orders reflect current expectations of outcome and not the ‘preventability’ of the preceding clinical events; (2) the majority of deaths in hospitalized children, especially in the ICU, occur some days after a clinical deterioration event [3,7,10,18,21,82], but within a relatively short time (hours) between DNR order and death [83-85]. Before confirming that a death in a patient with a DNR order was truly unpreventable, the clinical context and timeline of clinical deterioration prior to the DNR order must be known. It must also be recognized that medically ‘futile’ resuscitation may be performed on hospitalized children [86] for whom no DNR order is in place.

EPOCH outcomes are assessed for 1 year after hospital-wide implementation of intervention or continuation of standard care. This duration was chosen to reduce the effects of seasonal variation, but also to reduce the burden of a multi-year intervention period on each hospital, thus increasing feasibility, and to support timely completion of the study to support the decision-making needs of administrators. Continued eligibility will be confirmed by intermittent reporting of the MET-RRT and Early Warning Score use during the course of the study.

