### Sample size and assumptions

Power calculations are based on population estimates derived from 14 local hospitals’ data using a published method for cluster RCTs [61]. For all-cause mortality we found a baseline rate of 5.1/1000. The steering committee agreed that a mortality reduction of less than 1/1000 admissions would not be a compelling reason to modify practice. A study with 20 hospitals can show an 18% relative risk reduction in mortality (absolute risk reduction 0.09%), given alpha = 0.05 (2-sided), power = 80%, mean of 119 pediatric beds, length of stay = 4 days, with 0.90 average occupancy, k = 0.15, *n* = 20, baseline rate = 5.1/1000. The quantity k is the coefficient of variation for mortality between hospitals. Assuming attrition of 1-2 hospitals, we will include a sample of 22 hospitals.

Data from 4 pediatric hospitals in Ontario indicate there are 1052 urgent ICU admissions/year, of which we estimate 40% involve SCDE, for a rate of 2 per thousand patient days. Thus, with 20 sites we will be able to show a 31% reduction in SCDE [alpha = 0.05 (2-sided), power = 80%, k = 0.15, where k is the coefficient of variation for SCDE rate between hospitals]. The value of k allows for a moderate amount of clustering within hospital.

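### The power calculation implies about twice the admissions, patient-days and deaths that the Discussion expects, and its 80% power is not reached at either volume with 20 hospitals in total

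*Protocol article*

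**What the plan says.** Sample size and assumptions: "For all-cause mortality we found a baseline rate of 5.1/1000". It continues: "A study with 20 hospitals can show an 18% relative risk reduction in mortality (absolute risk reduction 0.09" per cent), with the inputs "given alpha = 0.05 (2-sided), power = 80%, mean of 119 pediatric beds, length of stay = 4 days, with 0.90 average occupancy, k = 0.15" and n = 20. It defines k: "The quantity k is the coefficient of variation for mortality between hospitals". The method is cited as a published one for cluster trials; no formula is printed. Twenty-two hospitals are to be included, to allow for the loss of one or two.

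Randomization: hospitals are allocated 1:1. Secondary outcomes (resource utilization): 26 baseline weeks, a 5-week run-in or break, then 52 weeks of outcome assessment.

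Discussion: the 22-hospital trial will "involve an estimated 100,000 patients admitted for about 400,000 patient-days and describe approximately 1900 urgent ICU admissions, 200 cardiac arrest events and 500 deaths". Table 6 repeats the patient count ("Obtaining consent is not feasible for 100,000 patients anticipated in the study sample"), and so does Planned conduct when it argues for waived consent.

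**The concern.** The beds, occupancy and stay in the sample size section fix the number of admissions per hospital, and that number helps determine the power. The Discussion then forecasts a much smaller trial in more hospitals. Both sets cannot describe the same trial, so the stated power cannot be carried over to the trial that the Discussion describes.

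The primary outcome is at stake. The same section says a reduction below 1 per 1000 admissions would not be a compelling reason to change practice, and the stated 18% of 5.1 per 1000 is 0.92 per 1000, so the trial was sized close to that threshold. The Limitations section says a negative result would allow the costs of implementation to be avoided. A reader weighing a negative result needs to know how likely the trial was to detect the effect it was sized for.

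**Working it through.** **1. Volumes implied by the sample size inputs** ("mean of 119 pediatric beds, length of stay = 4 days, with 0.90 average occupancy", taken over one year)

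- Patient-days per hospital: 119 × 365 × 0.90 = 39,092
- Admissions per hospital: 39,092 / 4 = 9,773

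| | Admissions | Patient-days | Deaths at 5.1/1000 |
|---|---|---|---|
| 20 hospitals, one year | 195,458 | 781,830 | 997 |
| 22 hospitals, one year | 215,003 | 860,013 | 1,097 |
| 10 hospitals, one year | 97,729 | 390,915 | 498 |
| Discussion, 22 hospitals | 100,000 | 400,000 | 500 |

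For 20 hospitals the ratios to the Discussion are 1.95, 1.95 and 1.99. If the 100,000 also covers the baseline weeks, the outcome year holds 100,000 × 52/78 = 66,667, about a third of 195,458. The Discussion figures nearly equal 10 hospitals for one year, which would be one arm of a 20-hospital trial. The article does not say that this is how they arose.

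**2. Formula assumed**

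The standard unmatched-cluster (Hayes-Bennett) formula, because the article expresses clustering through k:

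c per arm = 1 + (z_α/2 + z_β)² × [p0(1−p0)/m + p1(1−p1)/m + k²(p0² + p1²)] / (p0 − p1)²

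Here m is admissions per hospital, p0 = 0.0051 and p1 = 0.0051 × 0.82 = 0.00418. Results are also given without the leading 1.

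**3. The plan's own figure (80%)**

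At m = 9,773 and k = 0.15 the bracket is 5.19 × 10⁻⁷ + 4.26 × 10⁻⁷ + 9.79 × 10⁻⁷ = 1.924 × 10⁻⁶, and (p0 − p1)² = 8.43 × 10⁻⁷. Then c = 1 + 7.85 × 1.924/0.843 = 18.9 per arm (19.7 for an absolute reduction of exactly 0.09%).

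- 20 hospitals per arm: power 82%, detectable reduction 17.5%. This reproduces the stated claim.
- 10 per arm, which is 20 in total: power 51% (55% without the leading 1), detectable reduction about 24% to 25%.
- 10 per arm with k = 0: power 81%. This also reaches 80%, but the stated k is 0.15.

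**4. At the Discussion's 100,000 patients** (18% reduction, k = 0.15)

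| Hospitals per arm | Admissions per hospital | Power | Reduction detectable with 80% power |
|---|---|---|---|
| 10 | 4,545 (100,000/22) | 35.5% | 30.4% |
| 10 | 5,000 (100,000/20) | 37.4% | 29.6% |
| 11 | 4,545 | 38.7% | 29.0% |
| 10, without the leading 1 | 5,000 | 40.8% | 28.2% |

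On 5.1 per 1000, a 28% to 30% reduction is about 1.4 to 1.5 per 1000. If the 100,000 includes baseline, power is about 28% to 32%. With k = 0 it is about 49% to 57%.

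**5. Separating the two causes**

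- Moving from 20 per arm to 20 in total at full volume takes power from 82% to 51–55%.
- Moving from 195,000 to 100,000 patients takes it from 51–55% to about 35–41%.
- With 20 hospitals per arm and 5,000 admissions each, power would be 66%.

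**The case against.** **A planning estimate and a later forecast may differ.** The sample size inputs come from 14 local hospitals and the Discussion is an estimate for the trial, so some drift is natural. That is fair, and no enrolled volumes are shown. A reader might infer that the enrolled hospitals are half the planned size, but the documents do not establish this; the lower set could equally count one arm. The objection does not remove the need to say which volumes the power statement describes.

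**Patients are not admissions.** Repeat admissions could make the patient count smaller than the admission count. They cannot explain why patient-days and deaths are halved as well.

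**Baseline adjustment may reduce the effective k.** The primary model includes baseline mortality, so this is possible. At 100,000 patients even k = 0 gives at most about 57%.

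**The formula is an assumption.** This stands. Taking 20 as the number per arm reproduces the stated figures closely, which supports the choice but does not prove it.

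**Other figures agree with the lower volume.** A reader might scale "Data from 4 pediatric hospitals in Ontario indicate there are 1052 urgent ICU admissions/year" to 263 per hospital, expect about 5,800 in 22 hospitals, and see a further contradiction with the 1,900 stated. The documents do not support that. With 40% involving a significant clinical deterioration event (SCDE), at 2 per 1000 patient-days, those four hospitals have 1052 × 0.40 / 0.002 = 210,400 patient-days. That is 52,600 each, or about 160 beds at 0.90 occupancy, so they are larger than the 119-bed mean. The urgent admission rate is 1052/210,400 = 5 per 1000 patient-days, and 5 × 400 = 2,000, close to 1,900.

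Nor does the lower volume create a shortfall for SCDE. At 400,000/22 = 18,182 patient-days per hospital the detectable reduction is about 26% to 27%, which is better than the stated 31%.

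**The waiver does not depend on the factor of two.** Correct: individual consent is no more feasible for 100,000 than for 200,000.

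**Conclusion.** The point stands as two linked errors in the mortality power statement. The implied volumes are about twice those in the Discussion, Planned conduct and Table 6 (about three times if the lower figures include baseline), and nothing in the article reconciles them. Separately, the stated inputs with 20 hospitals in total give 51% to 55% power, not 80%. At 100,000 patients the figure is about 35% to 41%.

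A reader might infer that the smaller patient count alone explains the fall from 80%, and that restoring 195,000 admissions would restore the power. It would not: the larger part of the fall comes from the number of hospitals per arm.

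The result assumes the Hayes-Bennett formula, equal cluster sizes, k = 0.15, and 100,000 as the outcome-year total. If that total includes baseline, power is lower. The documents do not show which set of volumes is right.

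**What to change.** Adopt one set of volumes and use it in Sample size and assumptions, Planned conduct, Table 6 and the Discussion. State whether it covers the 52 outcome weeks only or also the 26 baseline weeks, and whether it counts one arm or both. State the formula and the number of hospitals per arm used, then restate the power for an 18% mortality reduction and the reduction detectable with 80% power.

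Keep the planning assumptions on record and label any update as such. Trial status reports that data collection had ended in 19 hospitals, so observed volumes could inform an update, but they should not silently replace the design inputs.

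The cost is a text correction and a short recalculation; the design and conduct do not change. The stated mortality power becomes less favourable if 20 is the total number of hospitals, and less favourable again if 100,000 is the right patient count.

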### Limitations of EPOCH

EPOCH has some limitations. First, by excluding the use other severity of illness scores, EPOCH will not provide data comparing alternate scores. This more refined question will need to be evaluated separately, preceded by appropriate studies to support selection of best comparators. Evaluation of the ‘best available’ system is important for proof of concept, needed before these more refined questions are addressed. Second, EPOCH does not assess quality of life, parental perceptions or neuro-cognitive outcome. All are relevant measures of the process and outcome of care [11]. In other prospective work we have shown that urgent ICU admission is associated with reduced health-related quality of life and acquired neuro-cognitive deficits [11]; thus, it would be reasonable to include these measures as outcomes in EPOCH. Exclusion of these elements was due to logistic constraints; acquisition of these data for all admissions would not be feasible, and following these urgent ICU admissions would be both resource intense and would require prospective consent/assent and follow-up. Finally, mortality may be both too coarse a measure and too infrequent an event to demonstrate clinically important differences.

EPOCH is a 22-hospital cluster-randomized trial evaluating the impact of the BedsidePEWS as a mechanism to improve the identification of children with evolving critical illness, reduce near and actual cardiopulmonary arrest, and reduce all-cause hospital mortality in hospitalized children. The results of this trial will provide a scientific basis for local, regional, provincial and national decision-making and for recommendations to national and international bodies [87], such as the AHA and European Resuscitation Council [88] about cardiac arrest prevention and institutional best practices.

If negative, the costs of hospital-wide implementation can be avoided, resources more appropriately allocated and the collaborative multi-site data set from the study used to develop and evaluate new hypotheses about cardiac arrest prevention and processes of care. If positive, then EPOCH will have provided a scientific justification for the major system-level changes required for implementation and supported the creation of evidence-based policy.

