**Discussion:**

Following funding by the Canadian Institutes of Health Research and local ethical approvals, site enrollment started in 2010 and was closed in February 2014. Patient enrollment is anticipated to be complete in July 2015. The results of EPOCH will strengthen the scientific basis for local, regional, provincial and national decision-making and for the recommendations of national and international bodies. If negative, the costs of hospital-wide implementation can be avoided. If positive, EPOCH will have provided a scientific justification for the major system-level changes required for implementation.

Trial registration: NCT01260831 ClinicalTrials.gov date: 14 December 2010.

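### A non-significant mortality result would not by itself rule out the 1/1000 reduction the steering committee set as its threshold, yet the article says a negative trial means implementation costs can be avoided

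*Protocol article*

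**What the plan says.** The abstract states what each outcome of the trial would mean: "If negative, the costs of hospital-wide implementation can be avoided" and "If positive, EPOCH will have provided a scientific justification for the major system-level changes required for implementation". The Limitations section repeats this at the end of the article and goes further on the negative side: "If negative, the costs of hospital-wide implementation can be avoided, resources more appropriately allocated". Neither place defines *negative*, and neither mentions a confidence interval or a size of effect.

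The size of effect that matters is given under Sample size and assumptions, where the steering committee agreed that "a mortality reduction of less than 1/1000 admissions would not be a compelling reason to modify practice". The same paragraph sets up a superiority calculation. The baseline is stated ("For all-cause mortality we found a baseline rate of 5.1/1000"), and 20 hospitals are said to be enough for an 18% relative reduction, shown as 0.09% absolute, "given alpha = 0.05 (2-sided), power = 80%, mean of 119 pediatric beds, length of stay = 4 days, with 0.90 average occupancy, k = 0.15". No equivalence or futility margin is stated.

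The Limitations section also concedes, in an earlier paragraph, that mortality may be too rare and too blunt an outcome to reveal differences of clinical importance.

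**The concern.** In a superiority design tested at two-sided 0.05, the ordinary meaning of *negative* is non-significant. Such a result says that no difference remains compatible with the data. It does not say that a worthwhile difference is incompatible with them. To conclude that hospitals can decline the intervention without losing a benefit they would care about, the interval has to exclude that benefit. The article puts it at 1/1000 admissions but does not use it when saying what a negative trial would mean.

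The article offers its results as a basis for decisions from local to national level and for international recommendations. If a non-significant result is read as the closing text suggests, a mortality reduction that meets the committee's own threshold could be set aside when the data have not excluded it.

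**Working it through.** **Inputs.** From Sample size and assumptions: baseline p0 = 5.1/1000; k = 0.15, where "The quantity k is the coefficient of variation for mortality between hospitals"; 20 hospitals (10 per arm at 1:1), 22 with allowance for attrition; two-sided alpha 0.05; 80% power. Admissions per hospital-year from beds, occupancy and stay: 119 × 0.90 × 365 / 4 = 9,773. From the opening of the Discussion: 100,000 patients in 22 hospitals, so 100,000 / 22 = 4,545 each. Counting all 100,000 in the intervention period is an assumption, and a generous one for precision.

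**The plan's own figure.** 18% of 5.1/1000 is 0.918/1000, which agrees with the stated 0.09%. The cited sizing method is not reproduced in the article. Under the usual unmatched cluster formula with k (an assumption), 10 hospitals per arm give a detectable reduction of 24.7% (1.26/1000), and 20 per arm give 17.5% (0.89/1000). So the stated 18% is not reproduced with 20 hospitals in total. That is a separate matter. Here the stated figure is taken at face value as one case.

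**Principle.** Count a reduction as positive and let h be the 95% half-width. A non-significant estimate can be as large as h, so its upper limit can be as large as 2h. A non-significant result can therefore include 1/1000 whenever h exceeds 0.5/1000.

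**Formulas.** Stated power: SE = 0.918 / (1.960 + 0.842) = 0.328/1000; h = 1.96 × 0.328 = 0.64/1000; lower end of the range 1 − 0.64 = 0.36/1000.

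Other cases, with c hospitals per arm and m admissions each: SE = sqrt({[p0(1−p0) + p1(1−p1)]/m + k²(p0² + p1²)}/c).
- Sizing inputs, no effect: sqrt(2 × (5.19 + 5.85) × 10⁻⁷ / 10) = 0.470/1000.
- 100,000 patients in 22 hospitals, no effect: sqrt(2 × (11.16 + 5.85) × 10⁻⁷ / 11) = 0.556/1000.

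For the ranges in the last column, p1 = p0 − d with each arm's own rate. The upper end solves d = q × SE(d), where significance begins. The lower end solves d + q × SE(d) = 1/1000. Here q is 1.960 (z), or t with 18 df (2.101) or 20 df (2.086).

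| Case (per 1000) | SE, no effect | h, no effect | Non-significant observed reductions whose CI includes 1/1000 |
|---|---|---|---|
| Stated power at face value | 0.328 | 0.64 (z) | about 0.36 to 0.64 |
| 9,773 per hospital, 10 per arm, k = 0.15 | 0.470 | 0.92 (z), 0.99 (t) | about 0.08 to 0.86 (z), 0.01 to 0.92 (t) |
| 4,545 per hospital, 11 per arm, k = 0.15 | 0.556 | 1.09 (z), 1.16 (t) | from below zero to 1.02 (z), 1.08 (t) |
| 4,545 per hospital, 11 per arm, k = 0 | 0.451 | 0.88 (z) | about 0.12 to 0.85 (z) |
| 9,773 per hospital, 11 per arm, k = 0 | 0.307 | 0.60 (z) | about 0.4 to 0.6 (z) |

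h exceeds 0.5/1000 in every row. The k = 0 rows bound what the planned adjustment for baseline mortality could gain by removing between-hospital variation.

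**How often.** The chance that a true reduction of 1/1000 comes out non-significant is about 14% at the stated power. It is 37 to 43% on the sizing inputs with 10 per arm, and 51 to 56% with 100,000 patients in 22 hospitals. With no true effect, the chance of a non-significant result whose CI still includes 1/1000 is about 11%, 41% and 54% in the first three rows (z, unadjusted in the second and third).

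**The case against.** The strongest reply is that these are closing remarks on impact, not an analysis rule. *Negative* is undefined, the wording is permissive, the data analysis section contains no adoption rule, and interpretation is left to the executive steering and writing committees with independent review before submission. The sentence can also be read as a default: do not pay for system-wide change until benefit is shown. On that reading nothing has to be excluded. This is right about the status of the text, and a reader who inferred a formal decision rule would be going beyond the article. But the remark appears in both abstract and conclusion, and it goes beyond saying that benefit was not shown.

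A second reply is that the article already concedes mortality may be too rare to show important differences. It does, but the concession is never linked to the sentence about a negative result. If it is true, it weakens that sentence.

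A third is that the larger figures depend on unadjusted precision and on setting the stated power aside. That is fair, and it is why the stated power is shown first. The problem is smaller there but still present.

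Two stronger readings are tempting and not supported:
- **A clear observed benefit, say 1.1/1000, would be called negative.** With 100,000 patients, k = 0.15 and each arm's own rate, significance starts at 1.02/1000 (z) or 1.08/1000 (t), so 1.1/1000 is significant. On the sizing inputs it starts below 1/1000.
- **The positive statement fails in the same way because the target of 0.92/1000 lies under the threshold.** With 100,000 patients and k = 0.15, no significant estimate can fall near 0.92/1000. At the stated precision one can (significance starts at 0.64/1000), but its interval would still contain 1/1000. A cut-off on the point estimate for a positive result would be a debatable preference.

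**Conclusion.** The point holds for the negative side. A non-significant result does not by itself support the conclusion that implementation costs can be avoided, because its 95% CI can contain the 1/1000 reduction the committee set as its threshold. This is so at the stated power, on the sizing inputs, at the projected 100,000 patients, and with between-hospital variation removed altogether. The extent runs from a band of about 0.36 to 0.64/1000 at the stated precision to every non-significant observed reduction at 100,000 patients with k = 0.15. A negative result whose CI excludes 1/1000 would support the sentence as written.

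The figures assume equal hospital sizes, a hospital-level comparison of proportions, and no gain from baseline adjustment except in the k = 0 rows. The planned weighted logit model would probably fall between the k = 0.15 and k = 0 rows. The primary test is unaffected; only the inference from a non-significant result needs changing.

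**What to change.** In the abstract and in the Limitations section, limit the statement about avoided costs to results whose 95% CI for the absolute difference in mortality excludes a reduction of 1/1000 or more. Describe any other non-significant result as inconclusive with respect to that threshold. Report the absolute difference per 1000 admissions with its CI beside the odds ratio from the primary model. No cut-off on the point estimate is needed for a positive result.

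The cost is a change of wording and one derived interval. Data collection was still open in some hospitals at submission, so the wording could be settled before the final analysis. The downside is that a sizeable share of trials with no true effect would be labelled inconclusive: about 11% at the stated precision, and 41 to 54% on the other inputs, unadjusted.
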